#### Data Analysis

The qualitative data from the in-depth interviews will be analyzed using a thematic approach. The in-depth interview data will be translated and transcribed, and then the transcripts will be read and reread for familiarization. Deductive coding will be conducted based on the aforementioned existing models, and an inductive coding strategy will be adopted when new factors emerge from the in-depth interview transcripts. At least 2 researchers will code and generate themes to explain the phenomena and facts. Member checking with the interview participants and peer debriefing will be conducted to improve the trustworthiness of the qualitative findings. The qualitative analysis software NVivo (version 12; Lumivero) will be used to facilitate coding and theme development.

### Ethical Considerations

The study received ethics approval (IHEC/CUK/2024/04) from the Institutional Human Ethics Committee of the Central University of Kerala on August 1, 2024. Informed consent from participants will be obtained upon their enrollment in the study. A personal identification number will be used to ensure the privacy of the participants. The recruited participants will be allowed to withdraw from the study at their request irrespective of the stage at which they are in the study. In case of any unforeseen medical emergencies, the participants will be guided to receive essential treatment from the nearest public health care facility. All the participants from the intervention and control groups will benefit from the intervention at the end of the study. The participants will not receive any financial or material compensation for taking part in the study.

### Clinical Trial Registration

The study was registered as a nonrandomized active-controlled trial (phase 1 and phase 2 combined) in the Clinical Trials Registry – India. This study protocol version was approved and received the registration number CTRI/2024/09/073166 on September 2, 2024.

## Results

All 240 participants were recruited by July 2025. The study completed data collection in August 2025 and is expected to finish data analysis by April 2026. The study results are expected to be submitted for publication in July 2026. The baseline survey will help understand the participant characteristics, medication status, lifestyle factors, and blood pressure measurements before the intervention. The intention to use the mHealth strategy for hypertension management is also measured at this stage. The follow-up survey data will provide the participant characteristics after the intervention phase. The baseline and follow-up survey data will allow us to study the effectiveness of the intervention on the medication and lifestyle variables. Furthermore, the in-depth interviews will help provide insights into the lived experiences of participants during the period of the intervention, focusing on the adaptation of the mHealth intervention for adherence to medication and a healthy lifestyle. The interviews will also enable the understanding of the perceived effectiveness of the intervention. The study has not received any funding.

## Discussion

### Expected Findings

The study will develop an mHealth strategy to improve medication and lifestyle adherence for hypertension management. WhatsApp was considered a suitable platform as it is cost-effective and user-friendly. Moreover, it does not need to be separately downloaded and subscribed to like other apps as most people already use it for regular messaging [10,11].

The study seeks to establish a proof of concept for a WhatsApp-led mHealth strategy that can be integrated into hypertension management at the community level. This strategy could function as a means for timely reminders and encourage individuals to change their behavior, improving medication adherence and lifestyle modifications [40]. Similar approaches could be adopted for individuals with other chronic noncommunicable diseases. Moreover, health care professionals, especially frontline health workers, can contact, provide information to, and receive updates from patients through WhatsApp as instant messaging platforms such as this one can facilitate mHealth services by acting as a medium for communicating health advice and hypertension management guidelines [5,6,9,12,13].

Selecting only 1 taluk from the Kannur district is a major limitation. However, considering that there are similarities in the sociodemographic and economic conditions, linguistic homogeneity (the predominant language is Malayalam), and commonalities in the political and administrative factors, the findings could be generalized to the context of Kerala as a whole. The study adopted a quasi-experimental study design with an intervention group and a control group because the main aspects of a randomized controlled trial, such as randomization, matching, and blinding, cannot be applied in this context. Unlike other trials, this study uses an mHealth intervention, which acts as a platform for sending hypertension awareness messages and reminders for a healthy lifestyle and medication adherence in addition to the routine hypertension care available in health centers. There could be limitations in establishing causal conclusions about the observed effects. However, the qualitative interviews with the participants who received the intervention could help obtain a deeper understanding of their experiences with and adoption of the intervention to adhere to a healthy lifestyle and medication.

The follow-up survey time point of 3 months after the intervention was determined based on the review period (ie, 3 months) for lifestyle and blood pressure measurement changes as per the hypertension management protocol of the Department of Health Services, Government of Kerala [24]. This duration of 3 months is also based on the minimum period required for behavior changes or to develop new habits, including physical activity and dietary changes [12,44,45]. The long-term sustainability of behavior change and the durability of the mHealth intervention will be explored through the qualitative interviews. Even though the intervention ends after 3 months, the ability to keep the messages for an indefinite time, as well as the option to create a backup in WhatsApp, allows the participants to go through the messages again if needed after the intervention period.

WhatsApp is a ubiquitous platform that is not primarily meant for medical communication. However, given the real-time nature of WhatsApp-based intervention and health messaging specific to the individual participant, this study is expected to be effective in improving adherence to medication and healthy lifestyle and have better participant engagement with the mHealth intervention.

The individualized delivery method, with a person-to-person (researcher-to-participant) messaging system rather than a WhatsApp group or community, will help minimize contamination between the intervention and control groups. Additionally, all participants will be recruited from their homes and monitored regularly during the follow-up period until the end-line survey. In addition, during sample size estimation, the researcher accounted for the cluster effect to obtain an adequate sample size to prevent the reduction in the samples’ power due to contamination.

The findings from the study will contribute to improving the planning and implementation of mHealth services for managing chronic diseases such as hypertension in India and other similar settings. Tailoring health messages specifically to the individuals could be challenging. However, prestructuring the messages will be helpful for easy dissemination. The researcher will recruit 4 batches of approximately 30 participants each into the control and intervention groups and then start sharing the messages individually with the participants in the intervention group. The entire intervention will be completed in these 4 batches. This is only for the convenience of the participants and the researcher to reduce the gap between the baseline survey and the first day of the intervention. The end-to-end encryption option of WhatsApp helps protect each individual’s chat data, and saving the participants’ contact information using code names will help protect their privacy.

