#### Sampling

The study followed a multistage cluster sampling method. In the first stage, all taluks in the Kannur district were listed, and then 1 taluk (ie, Payyanur taluk) was selected. One rural (ie, Karivellur-Peralam gram panchayat) and one urban (ie, Payyanur municipality) administrative unit (cluster) from this taluk were then selected for the study (Figure 2). In stage 2, a door-to-door household survey will be conducted in these 2 rural and urban clusters. Household members aged 40 to 59 years will be screened for eligibility after consent is obtained. In the third stage, eligible participants (those with hypertension and access to WhatsApp) will be surveyed. After the baseline survey, the study’s recruitment will follow a nonrandomized approach (Figure 3) without matching or blinding as these are not applicable in this study setting. Upon recruitment and consent, the first participant will be allocated to the intervention group, and the next participant will be allocated to the control group. The participants will be recruited into the intervention and control groups sequentially in a 1:1 ratio. This process will be conducted iteratively until the sample size of 240 is reached (ie, 120 in the intervention group and 120 in the control group). At the cluster level, this amounts to 120 participants per cluster (urban and rural), with 60 of them in the intervention group and 60 in the control group.

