**Figure 4. F4:**
[figure not shown]
WhatsApp-led mobile health intervention for medication and lifestyle adherence in participants with hypertension.

The diagnosis and treatment details of the study participants will be obtained during the baseline survey. Furthermore, the messages will be tailored considering their hypertension treatment status (ie, those who are under medication and those who are not under medication). Among those who are under medication, awareness of healthy lifestyles will be promoted, and they will receive reminders for proper medication adherence, regular consultation with their treating physician, and blood pressure monitoring. Newly diagnosed individuals with hypertension and those who are not in treatment will be sent health messages highlighting the need to adhere to positive health behaviors, consult a physician, and monitor their blood pressure periodically.

The messages for a healthy lifestyle include awareness and reminder messages for keeping healthy eating habits, focusing on the Dietary Approaches to Stop Hypertension diet. The messages also include the need for adequate physical activity and a list of physical activities classified by effort level (mild, moderate, and vigorous). Messages on the importance of reducing mental stress, quitting smoking, avoiding exposure to secondhand smoke, and controlling alcohol intake will also be shared with the participants.

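### Matching is called inapplicable although treatment status is known before allocation, and the stated analysis does not adjust for a chance imbalance in it

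*Protocol article*

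**What the plan says.** The Discussion (Expected Findings) gives as the reason for the quasi-experimental design that "the main aspects of a randomized controlled trial, such as randomization, matching, and blinding, cannot be applied in this context". The Sampling section of the quantitative phase says the same and also fixes the timing: "After the baseline survey, the study’s recruitment will follow a nonrandomized approach (Figure 3) without matching or blinding as these are not applicable". Neither place names an obstacle to matching.

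The allocation rule in Sampling is alternation: "the first participant will be allocated to the intervention group, and the next participant will be allocated to the control group". By cluster, "this amounts to 120 participants per cluster (urban and rural), with 60 of them in the intervention group and 60 in the control group". Treatment status plays no part in the rule.

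The Intervention section states that "The diagnosis and treatment details of the study participants will be obtained during the baseline survey", and that "the messages will be tailored considering their hypertension treatment status (ie, those who are under medication and those who are not under medication". The captions of Figures 5 and 6 show contact codes that separate physician-diagnosed participants on medication from cases found at screening. The Discussion describes recruitment in four batches of about 30 per arm, with messaging starting after a batch is recruited.

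The Statistical Analysis section plans a baseline comparison of the arms that covers health-related characteristics, between-arm tests with unadjusted odds ratios, and a GEE. The GEE terms named are time, intervention, their interaction and sociodemographic factors. Table 1 lists treatment details separately from sociodemographic characteristics.

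**The concern.** The claim that matching cannot be applied conflicts with the sequence the article describes. The treatment status of each participant is on record when the arm is assigned, and it is already used to sort participants into message streams. Separate 1:1 sequences by status, or pairing within a batch, needed no extra information.

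Treatment status is a natural balancing factor for two reasons. It decides the content of the intervention. It also bears on the expected course of blood pressure. Under the hypertension definition in Table 1, a diagnosed person enters whatever the reading, while an undiagnosed person enters only with SBP of at least 140 and/or DBP of at least 90 mm Hg. Selection on a high reading implies some regression to the mean in the second group. Table 1 places the blood pressure measurement under screening and follow-up, so the qualifying reading may also be the pre-intervention value, which would strengthen this effect.

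If the arms differ in mix, part of any difference in blood pressure change reflects the mix and not the messages.

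**Working it through.** **1. The plan's own figure.** Inputs from Sample Size: DBP 80.9 (SD 10.9) and 75.4 (SD 11.5), 80% power, 95% CI, design effect 1.5, 20% nonresponse.
- Difference: 80.9 − 75.4 = 5.5 mm Hg.
- Pooled SD: √((10.9² + 11.5²)/2) = 11.20.
- n per arm: 2 × (11.20 × (1.960 + 0.842)/5.5)² = 65.1, so 66.
- 66 × 1.5 = 99, and 99 × 1.2 = 119 per arm, against 120 stated. The figure reproduces to within rounding.

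**2. How mix enters the contrast.** Let p_I and p_C be the shares on medication in the two arms, and g the difference in expected blood pressure change between status groups, apart from the intervention. The between-arm difference in change then equals the intervention effect plus (p_I − p_C) × g. The time-by-intervention term removes a baseline difference in level but not this product. A main effect for status does not remove it either, because it shifts both time points equally. A status-by-time term, or a contrast within status groups, does.

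**3. Size of a chance imbalance.** Assumptions: order of recruitment is unrelated to status; p lies between 0.5 and 0.7 (not in the documents); 120 per arm. SD of p_I − p_C = √(2p(1−p)/120). The probabilities come from the exact difference of two Binomial(120, p) counts.

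| p | SD (points) | 95% range (points) | P(at least 10 points) |
|---|---|---|---|
| 0.5 | 6.5 | ±12.7 | 13.7% |
| 0.7 | 5.9 | ±11.6 | 10.5% |

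At p = 0.85 the SD falls to 4.6 points and the probability to 3.7%.

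**4. Effect on DBP.** Assumption: g = 5 to 10 mm Hg (not in the documents).
- A 10-point imbalance gives 0.10 × 5 = 0.5 to 0.10 × 10 = 1.0 mm Hg, or 9% to 18% of 5.5 mm Hg.
- At p = 0.5 the 95% range of the shift is ±0.6 mm Hg (g = 5) to ±1.3 mm Hg (g = 10).

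**5. Against sampling error.** SE of a difference in mean DBP with 120 per arm: 11.2 × √(2/120) = 1.45 mm Hg. The 10-point shift is 0.5/1.45 = 0.3 to 1.0/1.45 = 0.7 of one SE.

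**6. What balancing would have done.** Alternation by status within each cluster limits the arm difference to one person per cluster: 2/120 = 1.7 points, or 0.08 to 0.17 mm Hg for g = 5 to 10.

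**The case against.** Several objections have force.

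- **Allocation is finished.** The Results section says that all 240 participants were recruited by July 2025 and data collection ended in August 2025. A reader might infer that the remedy is separate allocation lists by treatment status. That can no longer help this trial.
- **Not stratifying is a choice, and stratification is not matching.** This is fair. The fault lies in the stated reason: the article says matching cannot be done when, on this factor, it could have been.
- **One list over all comers?** A reader might infer this from the alternation rule. The Sampling section gives 60/60 within each cluster, so the accurate statement is that alternation was not stratified by treatment status.
- **The effect is small and is chance, not bias.** If order of recruitment is unrelated to status, the shift is random variation already reflected in the standard error. This stands, and a claim of systematic bias from this source is not supported. Adjustment still removes the imbalance that actually occurred.
- **Every primary outcome is affected?** The documents do not show this. Nothing in them links treatment status to change in lifestyle, and no denominator is stated for medication adherence.
- **The grouping is imperfect.** People not on medication include both those found at screening and those diagnosed but untreated. The assumed gap, argued from selection on a high reading, may be smaller for the on/off medication split.
- **Covariates can be settled in an analysis plan.** The GEE list is introduced by way of example, and the baseline comparison should reveal an imbalance. But tabulating an imbalance does not adjust for it, and the terms that are named would not.

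Predictable, unconcealed alternation is a larger weakness, which balancing on status would not cure. The Discussion already concedes limits on causal conclusions.

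**Conclusion.** The point holds as a secondary weakness that can be remedied without new data. The statement that matching cannot be applied is unsupported for treatment status, which is known before allocation. The comparisons and model terms described do not deal with a difference in blood pressure change by that status.

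The size is modest: roughly a 10% to 14% chance of an imbalance of 10 points or more, which would move the DBP contrast by about 0.5 to 1.0 mm Hg. This rests on three assumptions: 50% to 70% on medication, a gap in change of 5 to 10 mm Hg, and recruitment order unrelated to status. The entry rule supports the existence of a gap, but its size is nowhere in the documents. The figures concern mean DBP, the measure used for the sample size, and do not extend to the adherence or lifestyle outcomes.

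**What to change.** 1. Tabulate baseline treatment status by arm within each cluster, showing screen-detected and diagnosed-but-untreated participants separately where numbers allow.
2. In the effectiveness analysis of blood pressure, include baseline treatment status and its interaction with time. Alternatively, form the arm contrast within the four cluster-by-medication-status cells and combine them with weights fixed in advance. Settle the choice before looking at outcomes by arm.
3. In Sampling and in Expected Findings, replace the statement that matching cannot be applied with a plain statement that allocation was by alternation within cluster, and was not matched or stratified by treatment status.

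The cost is a small amount of extra analysis and two wording changes. All the data needed are already collected, and the sample size does not change.

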#### Sample Size

A total study sample size of 240, with 120 each in the intervention and control arms, was estimated based on the estimates of diastolic blood pressure at baseline (mean 80.9, SD 10.9 mm Hg) and the postintervention time point (mean 75.4, SD 11.5 mm Hg) from a previous randomized controlled trial in Kerala [23]. *OpenEpi* was used for sample size calculation. The sample size was estimated at 80% power, a 95% CI, a 20% nonresponse rate, and a design effect of 1.5.

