#### Data Collection Tools and Techniques

Prospective participants will be screened using a checklist. Blood pressure will be measured as per the guidelines of the World Health Organization and the American Heart Association [29,30] using an Omron HEM-7113 blood pressure monitor [31,32]. The responses to the questionnaire will be self-reported by the participants. Lifestyle factors (ie, diet, physical activity, and tobacco use) and medication adherence will be assessed before and after the intervention period. Lifestyle factors will be assessed through a series of questions on fruit and vegetable intake, salt consumption, processed food intake, physical activity, tobacco use, and alcohol consumption. Medication adherence will be assessed using the Hill-Bone Medication Adherence Scale and a self-developed questionnaire to assess the reasons for nonadherence to medication [33,34]. The *KoboToolbox* application will be used along with the pen-and-paper approach to collect survey data. Additional physical measurements, such as waist and hip circumference, will be taken using the Seca ergonomic retractable tape at baseline and follow-up [31,32,35]. Both the baseline and follow-up surveys will be conducted at the participants’ homes. Responses to WhatsApp messages will be recorded in a Microsoft Excel spreadsheet throughout the intervention period. All the tools (Table 1) are prepared in English, translated into Malayalam, and back translated into English. Loss to follow-up will be managed through revisits and prescheduled interviews based on the participants’ convenience except in cases of refusal, migration, or death.

**Table 1. T1:** Data collection tools and techniques, along with the operationalization of variables.

Tool or technique and variable	Operationalization	References
Checklist for screening		
Eligibility factors	Age in years; self-reported pregnancy status, disability status, recent surgery, type 1 diabetes mellitus, and life-threatening diseases; access to a smartphone and WhatsApp via a “yes” or “no” question, and if yes, specify whose smartphone they have access to	[4,27,36]
Adapted questionnaires for the baseline survey		
Socioeconomic status	On the basis of the modified Kuppuswamy scale, a score of 26-29 indicates upper socioeconomic class, 16-25 indicates upper-middle socioeconomic class, 11-15 indicates lower-middle socioeconomic class, 5-10 indicates upper-lower socioeconomic class, and <5 indicates lower socioeconomic class	[37]

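### The Discussion credits the design effect for clustering with protecting power against contamination; the sample size has no such allowance, and the stated recruitment could place members of one home in opposite arms.

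*Protocol article*

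**What the plan says.** In the Discussion, under Expected Findings, the article gives two safeguards against contamination. The first is individual rather than group messaging. The second is the sample size: "the researcher accounted for the cluster effect to obtain an adequate sample size to prevent the reduction" in power that contamination would cause.

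The Sample Size section states its inputs as "80% power, a 95% CI, a 20% nonresponse rate, and a design effect of 1.5", applied to a change in diastolic pressure taken from an earlier trial, and arrives at "A total study sample size of 240, with 120 each in the intervention and control arms". Contamination is not among the inputs.

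The Sampling section of the quantitative phase describes a door-to-door survey in one rural and one urban cluster: "Household members aged 40 to 59 years will be screened for eligibility after consent is obtained". Allocation is by alternation: "the first participant will be allocated to the intervention group, and the next participant will be allocated to the control group". Each cluster ends with 60 participants per arm. No limit of one participant per household is stated.

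The screening checklist in Table 1 asks about access to a smartphone and WhatsApp and adds "if yes, specify whose smartphone they have access to".

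**The concern.** A design effect and contamination act on different quantities. A design effect inflates the sample because correlated observations carry less information; it concerns variance. Contamination shrinks the difference between arms; it concerns the size of the effect. Allowing for the first does not allow for the second.

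The recruitment as described makes contamination within the home plausible. The messages cover diet, salt, processed food, activity and secondhand smoke, which people who live together tend to share. Under alternation, two members of a home who are recruited one after the other must be placed in opposite arms. Individual messaging prevents leakage through a group chat but not through a shared kitchen or a shared phone.

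What is at stake is how a small or null result is read. A reader who accepts the sentence in the Discussion would think that contamination had been dealt with.

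**Working it through.** **Inputs (Sample Size section).** Baseline: "estimates of diastolic blood pressure at baseline (mean 80.9, SD 10.9 mm Hg"). Follow-up: "postintervention time point (mean 75.4, SD 11.5 mm Hg"). The difference is 80.9 - 75.4 = 5.5 mm Hg, and the sum of variances is 10.9² + 11.5² = 251.06. Power is 80%, two-sided alpha 0.05 (from the 95% CI), design effect 1.5 and nonresponse 20%.

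**Reproducing the plan's figure.** Base n per arm = 251.06 x (1.960 + 0.842)² / 5.5² = 65.1, rounded up to 66. Then 66 x 1.5 x 1.2 = 118.8, or 119 per arm, against the stated 120. Dividing by 0.8 instead of multiplying by 1.2 gives 123.75, or 124. Without the design effect the result is only 79.2 to 82.5 per arm. The stated size is therefore base n, clustering and nonresponse, with no further term.

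**What contamination would need.** If a fraction c of the difference is lost, n must be multiplied by 1/(1 - c)²: 1.23 at 10%, 1.56 at 20%, 2.04 at 30%. With the design effect kept and nonresponse as x 1.2, that is 146, 184 and 240 per arm.

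**Power under dilution.** The documents give no share of mixed-arm homes and no spillover, so c is an assumption, shown from 5% to 20%. As a guide, c is the share of controls exposed times the fraction of the effect they pick up: 10% of controls at half the effect is 5%, and 40% at half is 20%. With 120 enrolled and 20% lost, 96 per arm are analysed. If the design effect is really needed, that is 96/1.5 = 64 effective per arm. If clustering cancels because both arms sit inside each cluster, it is 96. Power = Φ(5.5(1 - c)/√(251.06/n) - 1.96).

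| Dilution c | Expected difference (mm Hg) | Power, n = 64 | Power, n = 96 |
|---|---|---|---|
| 0 | 5.50 | 79% | 92.5% |
| 5% | 5.23 | 75% | 90% |
| 10% | 4.95 | 71% | 86% |
| 15% | 4.68 | 66% | 82% |
| 20% | 4.40 | 60% | 78% |

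If the factor of 1.5 were entirely spare, it would offset a dilution of up to 1 - 1/√1.5 = 18% in power. The second column is the same whatever n is: the bias does not depend on sample size.

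**Standard errors.** For a pair in opposite arms with outcome correlation ρ > 0, the variance of the within-pair difference is 2σ²(1 - ρ). An analysis that treats the two as independent uses 2σ², so it would tend to overstate the standard error.

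**The case against.** The strongest reply is that the sentence speaks only of power, not bias, and that the extra sample may protect power in practice. With 60 and 60 in each of two clusters, the cluster effect should largely cancel in the comparison of arms. The factor of 1.5 is then spare, and power stays above 80% at 15% dilution. This stands as arithmetic, and it is why both columns are shown. It does not support the stated reason: the allowance was made for clustering, and it can serve contamination only to the extent that clustering does not need it. It also leaves the bias untouched.

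A reader might infer that mixed-arm households certainly exist. The article does not say so. It describes who is screened, not how many per home are enrolled, and the full protocol may hold a limit that the article omits. A reader might also infer that another person's phone was accepted for eligibility. Table 1 only records whose phone it is. Nor can it be said that contamination takes power below target, since that depends on an unknown dilution and on whether the design effect is needed.

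The spillover may also be modest. Messages are tailored to treatment status, and personal medication reminders pass less readily between people than meals do. Finally, the choice of GEE cluster and sensitivity analyses is often left to an analysis plan. Their absence from the article is not the fault raised here; they are offered as remedies.

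**Conclusion.** The sentence in the Discussion is wrong as a justification, even if no household turns out to be mixed. The sample size arithmetic itself is sound and reproduces; what fails is the property claimed for it.

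The household route to contamination is conditional: it follows from the stated screening and alternation only if more than one person per home was enrolled. Its size cannot be determined from the article. Over the assumed range, the loss of power runs from about 4 to 19 percentage points if the design effect is needed, and from about 3 to 15 if it is not, with the estimate biased toward no effect by 5% to 20%. These figures take the plan's 5.5 mm Hg as the true difference between arms and 20% as the true loss. A null or small result should not be interpreted as though contamination had been covered.

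**What to change.** Recruitment and data collection are complete, so allocation cannot change. Analysis is expected to run to April 2026, so the following is still possible.

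- Delete the statement that the cluster adjustment protects power against contamination. State instead that contamination was not allowed for in the sample size and would bias the comparison toward no effect.
- Where household can be linked from the home surveys, make it the cluster in the planned GEE model, with robust standard errors and each participant's two visits nested within it.
- Report the number of households with participants in both arms and, from the screening checklist, the number of participants who share a phone.
- Add one sensitivity analysis that excludes mixed-arm and shared-phone households.

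The cost is the work of linking households, which the article does not confirm were recorded in linkable form, and a smaller sample in the sensitivity analysis. If the count of mixed-arm homes and shared phones is close to zero, the count alone largely settles the matter.
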